#### Passive app

Participants are asked to download the RADAR-base passive remote monitoring app, configured for ART requirements [32], which runs in the background, requiring no further input from participants. The Passive App collects data on ambient noise, ambient light, phone usage information (e.g., which apps were used and for how long, when the phone was unlocked), passive audio, Global Positioning System (GPS) location, Bluetooth connectivity, battery life, gyroscope data, steps, and acceleration. Features of the passive audio, rather than raw audio itself, are extracted from the audio on the phone for transmission. GPS location data are randomised; that is, providing relative location data, not absolute coordinates. This prevents the identification of an individual’s home address or precise geographical location.

#### Wearable sensors

The wearable device in ART-transition is a low-cost, widely available, wrist-worn fitness tracking device (Fitbit Charge 6). Participants are asked to wear the device for the duration of the study (24 months), which provides ongoing data collection of physical activity, sleep, heart rate, breathing rate and skin temperature. Device sensors include a gyroscope, accelerometer, thermometer and photoplethysmographic pulse oximeter. Intraday series include activity metrics (per 1 min), heart rate (per 1 s), SpO2 (per 1 min), and breathing rate (per 1 min). The activity tracking feature records step count, distance travelled, floors climbed, elevation and intensity minutes (Metabolic Equivalent of Task, MET). Sleep statistics include the duration of sleep, sleep levels, sleep efficiency, time to sleep, and time in bed after waking. Data are collected from the Fitbit representational state transfer application protocol interface (REST-API) using the RADAR-base platform.

### Follow‑up procedure and data monitoring

Participants are contacted by telephone one month after their baseline assessment to address any concerns or questions. Brief follow-up phone calls are then offered every three months to maintain engagement with participants throughout the course of the study and to remind participants of any upcoming assessments. Participants are encouraged to live their lives as normal, responding to the Active App notifications when required. The research team are able to review if data is coming through using the RADAR-base management portal. The research team may contact participants if there is a loss of data from a device.

### Study debrief

At the end of the follow-up period (24 months), participants will receive a ‘debrief’ session, which will serve to collect endpoint acceptability and usability outcomes and to retrieve study materials (devices, chargers, etc.). This will be done either over the phone or on Microsoft Teams with a member of the research team and will be audio recorded using Microsoft Teams. Participants will also have an opportunity to view and discuss summaries of their data.

### Adverse events and study withdrawal

There may be several reasons for withdrawal from the study:

Participant choosing to no longer participate: Participants will be informed both in writing and verbally that participation is voluntary, that non-participation will not influence their medical care, and that they are free to withdraw from the study at any point without providing reasons.The research team may withdraw the participant in the event of intercurrent illness, adverse event (AE), protocol violation, administrative or other reasons.

In the event of participant self-withdrawal, all attempts will be made to follow up with the participant to establish the cause of withdrawal and to collect qualitative data regarding the experience of participation. All data, including those from withdrawn participants, will be included in the final analysis. If a participant withdraws from the study prematurely, we will consider replacing the participant if resources allow and if recruitment is ongoing for the study.

### Analysis plan

This study will generate rich longitudinal data across domains, including ADHD symptoms and impairment, co-occurring mental health problems, digital and cognitive markers, life transitions, and lifestyle behaviours, enabling a range of analyses. We will calculate descriptive statistics for participant demographics and RMT engagement, estimate attrition rates, and explore whether baseline characteristics predict drop-out or whether RMT data availability predicts subsequent outcome completion.

For Aim 1, we will examine how ADHD-related and contextual variables change and covary over time. We will visualise trajectories, estimate within- and between-person variance using generalised linear mixed models, and model individual-level change using spline-based random slope models. We will also examine how specific variable pairs covary over time—e.g., ADHD symptoms/impairment with co-occurring psychiatric symptoms, and with digital and cognitive markers. For each pair, we will estimate lagged associations using linear mixed models, distinguishing within- from between-person effects. This will allow us to identify dynamic patterns of change and factors that precede symptom fluctuations.

For Aim 2, we will develop multivariable prediction models for key outcomes identified in Aim 1, using regularised regression (elastic net) and tree-based machine learning (e.g. XGBoost). Model performance will be assessed using repeated, nested temporal cross-validation, with all modelling steps (e.g. pre-processing, imputation) repeated within each split to prevent data leakage. Models will include relevant baseline characteristics and participant-level covariates. To inform the development of a digital tool (Aim 3), we will build models that predict current-month outcomes based on predictors from preceding months (e.g. 1–3 months prior), incorporating lagged predictors and derived metrics such as changes in symptom severity or sleep variability.

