### Study population

The sample sizes were determined by simulation and analytical methods. For Aim 1, we considered power to detect associations between pairs of variables (e.g., ADHD symptoms and digital markers), provide precise of estimates of within-person variance and intraclass correlation (ICC), and the impact of missing data. For Aim 2, we estimated the sample size needed to develop multivariable prediction models (based on an expected model performance of R² ≈ 0.5 and 20 model parameters). Full details are provided in the Supplementary Materials. Overall, a sample of 250 participants (each providing monthly outcome assessments and continuous RMT data collection) will be sufficient to detect associations and estimate within-person variance with precision (Aim 1), even under conservative assumptions about missing data. This sample will be adequate to develop multivariable prediction models. Table 1 summarises the study eligibility criteria.

**Table 1 Tab1:** Eligibility criteria for participation in ART-transition

Participant inclusion criteria	1	Diagnosis of DSM-5 ADHD
	2	Aged 16–17
	3	Able to give informed consent for participation
	4	Willing and able to complete self-reported assessments via smartphone
	5	Willing to use either their own compatible Android phone or a study Android phone as their only smartphone during the data collection period
	6	Willing to wear the wearable device (Fitbit) during the data collection period
Participant exclusion criteria	1	Psychosis, currently experiencing a major depressive episode, mania, drug dependence in the last six months, or a major neurological disorder
	2	Recent contact with psychiatric acute care (admission, crisis team or liaison team (A&E)) in the last six months
	3	Any other major medical disease which might impact upon the patient’s ability to participate in normal daily activities (e.g., due to hospitalisations)
	4	Pregnancy
	5	IQ < 70
Informant inclusion criteria	1	A parent or guardian, as chosen by the participant with ADHD
	2	Aged 18 or over
	3	Willing and able to complete web-based questionnaires regarding the participant with ADHD

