## Discussion

ART-transition will provide a unique set of active and passive remote monitoring data over 24 months from young people with ADHD as they transition to adulthood. The fine-grained data on fluctuations and changes in multiple outcome measures, and their wide-ranging potential predictors, will enable analyses in different timescales from hourly or daily changes for some measures, to monthly changes for others. No comparable prior dataset exists, with past ADHD follow-up studies incorporating limited data collection timepoints and measures.

Our extensive PPI work has indicated the need for new self-management tools for ADHD. People with lived experience highlighted the importance of technologies augmenting clinical services rather than replacing them, and noted that an app they could use personally would be helpful. Furthermore, evidence from other areas of adolescent development and mental health shows that adolescents use and want smartphone apps and websites to support healthy lifestyle knowledge and behaviours [60] and place more trust and value on evidence-based resources [61]. This study, therefore, allows us to identify real-world targets for intervention that can be integrated into a prototype of a smartphone app, which will be co-developed during the study. We will develop a prototype smartphone app for young transition-age people with ADHD. The app will aim to prevent negative outcomes and support healthy lifestyles in young people with ADHD by facilitating self-management, personalisation of treatment and engagement with adult services. Our approach will focus on giving young people with ADHD greater autonomy in how they manage their ADHD, in collaboration with their clinician. It will emphasise modifiable environmental factors and the prevention of negative outcomes. The unique data collection, ART system, RADAR-base platform, and our extensive co-design team – including young people with ADHD, the PPI panel, healthcare professionals involved in the clinical care of young people with ADHD, MindTech and The Hyve (a leading IT and data services provider in life sciences [62])– place us in a unique position to design a prototype for a new smartphone app.

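### Aim 2 validation names only temporal splitting; unless whole participants are also held out, performance describes known participants and can be optimistic for new app users

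*Protocol article*

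**What the plan says.** The Analysis plan section of the protocol article describes Aim 2 as multivariable models fitted by elastic net and by tree-based learners such as XGBoost. On validation it says: "Model performance will be assessed using repeated, nested temporal cross-validation", "with all modelling steps (e.g. pre-processing, imputation) repeated within each split to prevent data leakage". On predictors it says: "Models will include relevant baseline characteristics and participant-level covariates". The models forecast the current month from roughly the one to three months before it, "incorporating lagged predictors and derived metrics such as changes in symptom severity or sleep variability".

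The section does not say whether all of a participant's months stay on one side of a split. It describes no held-out participants and no external sample.

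Study objectives makes validation part of Aim 2 and passes the influential predictors and their timing to Aim 3. The Discussion states the use: "We will develop a prototype smartphone app for young transition-age people with ADHD".

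**The concern.** The data are a panel: 250 people with monthly outcomes over 24 months, so up to 250 × 24 = 6,000 rows, strongly clustered by person. An ordinary temporal split of such data puts the same people in training and test sets. The models also contain covariates that do not change within a person. Taken together, these can come close to identifying an individual, and a tree learner can use them to store each person's usual level. Test performance then partly measures recognition of people already seen.

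The stated safeguard, refitting the modelling steps within each split, addresses a different leak. It stops test data from influencing imputation or scaling. It does nothing about a person who appears on both sides.

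Two things are at stake. The performance figure may not carry over to young people outside the cohort. The ranking of predictors that feeds Aim 3 may also favour stable characteristics that merely identify participants.

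**Working it through.** **The plan's own figure.** The only Aim 2 figures are in Study population: 250 participants, expected R² about 0.5, 20 parameters. The article does not name its formula, so the standard criteria for a continuous outcome were used, with P = 20 and R² = 0.5:

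- Residual SD estimated within 10% (chi-square limits on n − P − 1 degrees of freedom): n = 254.
- Expected shrinkage of at least 0.9, S = 1 + (P − 2)/(n·ln(1 − R²app)). At n = 230, R²app = (0.5 × 209 + 20)/229 = 0.544 and S = 1 − 18/(230 × 0.785) = 0.90.
- R² optimism of at most 0.05, as (1 − R²)·P/(n − 1). At n = 202 this is 0.5 × 20/201 = 0.0498.

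The largest, 254, is within 2% of 250. The sample size is not at fault.

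**Effect of the split.** The article gives no ICC or variance shares, so these are assumptions, with the ICC shown over a range. The main simulation used:

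- 250 people and 24 months. Models were trained on earlier months and tested on the last 6, with 6 replicates per setting.
- 10 baseline covariates explaining 10% of between-person variance.
- 7 digital predictors, entered as the previous month's value and its one-month change.
- Elastic net with cross-validated penalty, and XGBoost with fixed settings.
- The person's own outcome at lags 1 to 3 either included or left out.

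Test R² = 1 − Σ(y − ŷ)²/Σ(y − ȳ)². Optimism = R² with time-only splits minus R² with 5-fold participant groups also held out. Differences are taken before rounding.

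| Own lagged outcome | Learner | ICC | Time only | Time + participants held out | Optimism |
|---|---|---|---|---|---|
| Yes | Elastic net | 0.3 | 0.36 | 0.36 | 0.01 |
| Yes | Elastic net | 0.5 | 0.52 | 0.52 | 0.00 |
| Yes | Elastic net | 0.7 | 0.70 | 0.70 | 0.00 |
| Yes | XGBoost | 0.3 | 0.34 | 0.29 | 0.05 |
| Yes | XGBoost | 0.5 | 0.51 | 0.46 | 0.04 |
| Yes | XGBoost | 0.7 | 0.69 | 0.67 | 0.02 |
| No | Elastic net | 0.3 | 0.10 | 0.06 | 0.04 |
| No | Elastic net | 0.5 | 0.11 | 0.04 | 0.06 |
| No | Elastic net | 0.7 | 0.12 | 0.03 | 0.09 |
| No | XGBoost | 0.3 | 0.27 | −0.02 | 0.30 |
| No | XGBoost | 0.5 | 0.46 | −0.05 | 0.50 |
| No | XGBoost | 0.7 | 0.66 | −0.08 | 0.74 |

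A model that knew only each person's mean would reach an R² about equal to the ICC. The time-only XGBoost figures without own lags (0.27, 0.46, 0.66) lie close to 0.3, 0.5 and 0.7. At ICC 0.5, recognition of known people alone therefore nearly delivers the planned R² of about 0.5, while R² for new people is about zero.

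**Pure-noise covariates.** Two further simulations used tree models with covariates unrelated to the outcome, at ICC 0.5 and 0.7.

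- *Without own lags.* The first gave 0.37 against −0.20 and 0.62 against −0.24, so gaps of 0.57 and 0.86. The second gave 0.41 against −0.01 and 0.64 against −0.20, so gaps of 0.42 and 0.84. Any positive R² here can come only from recognising people.
- *With own lags.* The first gave 0.34 against 0.25 and 0.61 against 0.56, so gaps of 0.09 and 0.05. The second gave 0.40 against 0.34 and 0.64 against 0.59, so gaps of 0.06 and 0.05.

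**Limits.** In the main simulation the held-out models train on 200 people rather than 250, so some of each gap may reflect the smaller training set. The XGBoost settings were fixed, so the effect of participant overlap on inner-loop tuning was not measured.

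**The case against.** The strongest reply is that the article never says splitting is by time alone. It is silent on participant grouping, and its reference to repetition is compatible with random participant folds crossed with time. A condensed article may also leave fold construction to a fuller plan. This stands. A reader might infer that the plan definitely mixes participants across folds and that its reported performance is therefore inflated; the text supports neither as fact.

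A reader might also infer that the plan offers its temporal scheme as protection against this overlap. It does not. The remark about leakage is attached to repeating the modelling steps within each split.

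On size, the large gaps arise for tree models without the person's own earlier outcome. The plan uses preceding months and mentions changes in symptom severity, so some earlier symptom information will be present. With own lags the gap is small, and for elastic net it is close to nil. This stands too, although the plan does not say that the outcome's own earlier level is a predictor, and a change score carries little of a person's level.

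Temporal validation is also legitimate for forecasting later months in someone already monitored, which suits a self-management tool. The Discussion says the app will stress modifiable environmental factors, so fixed traits are unlikely app targets, and no passage says the fitted models will score new users. These points limit the harm. They do not remove it, because the results are directed to transition-age young people generally and predictor rankings are to feed Aim 3.

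**Conclusion.** The point holds in conditional form. The validation scheme as named splits on time. Followed literally on these data, it leaves the same people in training and test sets, and the stated safeguard does not address that. Performance would then be valid for future months of known participants and could be optimistic for new ones.

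Under assumed ICCs of 0.3 to 0.7, optimism in R² is about 0.00 to 0.01 (elastic net) and 0.02 to 0.09 (trees) when the person's own lagged outcome is a predictor. Without it, optimism is about 0.04 to 0.09 (elastic net) and from 0.30 to 0.86 across the tree simulations. The direction is consistent; the size rests on the learner, the predictor set and the assumed ICC. Because the bias differs by learner, a time-only comparison can also favour trees over elastic net for the wrong reason.

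The documents do not support the stronger claim that the reported performance will be materially inflated whatever the model.

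**What to change.** State in the Analysis plan that outer and inner folds are grouped by participant within the temporal scheme: train on earlier months of some participants and test on later months of others, with all rows of a person in one fold. Use this participant-held-out estimate for any claim about new users and for choosing predictors for Aim 3. Report the time-only estimate separately, labelled as performance for future months of known participants.

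If a fuller plan already groups by participant, one clause in the article settles the matter. Otherwise the change is a sentence or two, made before modelling starts, and needs no new data. The cost is more computing and a possibly lower reported performance.

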### Data protection

Data acquired from the wearable devices and the RADAR-base Active and Passive Apps will be encrypted, pseudonymised, and uploaded automatically via Wi-Fi to secure, GDPR compliant servers managed by the RADAR-base and research team. Digital data from other sources, including limited identifiable data and pseudonymised data, will be stored securely on a GDPR-compliant, secure storage provider. Physical data, e.g. from cognitive ability tests, will be stored in local storage at King’s College London before being uploaded to a GDPR compliant, secure storage provider.

## Discussion

ART-transition will provide a unique set of active and passive remote monitoring data over 24 months from young people with ADHD as they transition to adulthood. The fine-grained data on fluctuations and changes in multiple outcome measures, and their wide-ranging potential predictors, will enable analyses in different timescales from hourly or daily changes for some measures, to monthly changes for others. No comparable prior dataset exists, with past ADHD follow-up studies incorporating limited data collection timepoints and measures.

Our extensive PPI work has indicated the need for new self-management tools for ADHD. People with lived experience highlighted the importance of technologies augmenting clinical services rather than replacing them, and noted that an app they could use personally would be helpful. Furthermore, evidence from other areas of adolescent development and mental health shows that adolescents use and want smartphone apps and websites to support healthy lifestyle knowledge and behaviours [60] and place more trust and value on evidence-based resources [61]. This study, therefore, allows us to identify real-world targets for intervention that can be integrated into a prototype of a smartphone app, which will be co-developed during the study. We will develop a prototype smartphone app for young transition-age people with ADHD. The app will aim to prevent negative outcomes and support healthy lifestyles in young people with ADHD by facilitating self-management, personalisation of treatment and engagement with adult services. Our approach will focus on giving young people with ADHD greater autonomy in how they manage their ADHD, in collaboration with their clinician. It will emphasise modifiable environmental factors and the prevention of negative outcomes. The unique data collection, ART system, RADAR-base platform, and our extensive co-design team – including young people with ADHD, the PPI panel, healthcare professionals involved in the clinical care of young people with ADHD, MindTech and The Hyve (a leading IT and data services provider in life sciences [62])– place us in a unique position to design a prototype for a new smartphone app.

A key challenge for RMT studies is missing data due to non-compliance from participants, such as participants not answering questionnaires on the Active App or not wearing the wearable device. To mitigate missing data, we have introduced regular automated app notifications and integrated feedback from our PPI focus groups (e.g. sending more notification reminders, sending notifications at the same time each day, and limiting the number of times participants are asked to complete cognitive tasks).

By using RMT in transition-age young people with ADHD to carry out unobtrusive, real-time data collection over a period of 24 months and by co-designing a prototype ADHD-transition digital tool, we will address the core questions of what changes take place during the transition to adulthood, what predicts such changes, and how can we prevent negative outcomes and support healthy lifestyles.

## Data Availability

No datasets were generated or analysed during the current study.

## Abbreviations

ADHD: Attention Deficit Hyperactivity Disorder
ART: ADHD Remote Technology
DSM-5: Diagnostic and Statistical Manual of Mental Disorders, Fifth Edition
RMT: Remote Measurement Technology
PPI: Patient and Public Involvement
CAMHS: Child and Adolescent Mental Health Services
